**Figure 1 fig1:**
[figure not shown]
Flowchart of the trial intervention. ML, machine learning; YJT, *Yijung-tang*; PWS, *Pyeongwi-san*; SST, *Shihosogan-tang*; GIS, gastrointestinal symptom.

**Table 1 tab1:** Clinical study schedule.

Assessment	Visit 1 (screening)	Visit 2 (baseline, week 0)	Visit 3 (week 2)	Visit 4 (week 4)	Visit 5 (week 6)	Visit 6 (week 8)
Written consent						
Demographic/medical history survey	●					
Physical measurements	●					
Vital sign measurements	●	●		●		●
Blood test	●					
Confirmation of inclusion / exclusion criteria	●					●
Random allocation		●				
Concomitant medications and adverse reaction confirmation		●	●	●	●	●
Gastrointestinal Symptom Score	●			●		●
Total Dyspepsia Symptom Score	●			●		●
Adequate relief of dyspepsia			●	●	●	●
Overall treatment effect				●		●
Dyspepsia Visual Analog Scale	●			●		●
Functional dyspepsia–related quality of life	●			●		●
Spleen Qi Deficiency Questionnaire	●			●		●
Stomach Qi Deficiency Questionnaire	●			●		●
Food Retention Questionnaire	●			●		●
Cold–Heat Pattern Questionnaire	●			●		●
Deficiency–Excess Pattern Questionnaire	●			●		●
Standard Tool for Pattern Identification of FD	●					
Korean medicine diagnosis (interview, tongue, pulse, abdominal)	●			●		●
Clinical trial medication prescription and administration education		●		●		
Clinical trial medication returns and compliance check				●		●
Stool kit and meal record sheet provision	●			●		
Stool sample collection, meal record sheet confirmation, and saliva sample collection		●				●
Confirmation of clinical study completion						●

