### Sample size calculation

2.7

Participants will be randomly assigned to either the ACCORD group, which will receive YJT, PWS, or SST based on the machine learning–driven prediction, or the DISCORD group, which will not use the machine learning-based prediction for herbal assignments. Based on preliminary clinical trial results (19), the mean change in the GIS score after 8 weeks in both the ACCORD and DISCORD groups is assumed to be 2.72, with a standard deviation of 4.57. To meet this requirement, each group will require 45 participants. Considering a 10% dropout rate, the total required sample size is 100 participants. This sample size was determined for the prespecified primary comparison (ACCORD vs. pooled DISCORD) and was not inflated to power subgroup or stratified analyses, which will be considered exploratory.

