### Statistical analysis

2.8

All statistical analyses will be conducted using two-sided tests with a significance level of 5%. For continuous data, means and 95% confidence intervals will be presented, whereas categorical data will be presented as frequencies and percentages. All analyses will be performed using SAS® Version 9.4 (SAS Institute Inc., Cary, NC, United States).

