#### Statistical analysis and evaluation of efficacy endpoints

2.8.2

The primary efficacy endpoint is the between-group difference in the GIS score at week 8 (ACCORD vs. DISCORD). The primary endpoint will be analyzed using the MMRM, with treatment group and visit time as fixed factors and participant as a random factor.

The secondary efficacy endpoints include TDS, AR for dyspepsia, OTE, dyspepsia VAS, FD-QoL, Spleen Qi Deficiency Questionnaire, Stomach Qi Deficiency Questionnaire, Food Retention Questionnaire, Cold–Heat Pattern Questionnaire, and Deficiency–Excess Pattern Questionnaire. Categorical secondary variables will be analyzed using the chi-square test or Fisher’s exact test.

To address the issue of multiple comparisons for the multiple secondary efficacy endpoints, the Benjamini-Hochberg procedure (False Discovery Rate, FDR) will be applied to adjust the *p*-values. The primary endpoint will be tested at a significance level of 0.05 without adjustment. Exploratory outcomes will not be adjusted for multiplicity, and their results will be interpreted as hypothesis-generating.

Exploratory subgroup analyses (by assigned herbal formula and by DISCORD subgroup) will be performed to assess the consistency of treatment effects; these analyses are hypothesis-generating and are not powered for confirmatory inference. Effect modification will be explored using treatment-by-subgroup interaction terms within the mixed model, and results will be reported as effect estimates with 95% confidence intervals and interpreted cautiously.

For the primary outcome, missing data will be handled using the last observation carried forward (LOCF) method. In addition, multiple imputation will be applied as a sensitivity analysis to assess the robustness of results under different assumptions regarding missingness. The main analyses will be conducted on an intention-to-treat basis, with per-protocol analyses performed for comparison.

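### If the random participant term is the only covariance term, a week-8 contrast takes its standard error from a variance pooled over visits; the group-by-visit term it needs is not listed

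*Protocol article*

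**What the plan says.** Section 2.8.2 of the protocol article names the endpoint: "The primary efficacy endpoint is the between-group difference in the GIS score at week 8 (ACCORD vs. DISCORD". The next sentence gives the model: "The primary endpoint will be analyzed using the MMRM, with treatment group and visit time as fixed factors and participant as a random factor". No group-by-visit term is listed. The participant random factor is the only term that deals with within-participant correlation, and no residual covariance structure is named.

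The row "Gastrointestinal Symptom Score" in Table 1 shows GIS measured at screening, week 4 and week 8, so there are two post-baseline visits. On error control, section 2.8.2 says: "The primary endpoint will be tested at a significance level of 0.05 without adjustment". Section 2.8 makes all tests two-sided.

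The only GIS standard deviation in the document is in section 2.7, "with a standard deviation of 4.57", and it refers to the 8-week change. No SD is given for screening or week 4.

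**The concern.** A random participant intercept with independent, equal-variance residuals (the SAS default) is compound symmetry: the same variance at every visit and one correlation between any two visits. The week-8 contrast is an estimate at one visit. Under that structure its standard error comes from the average of the visit variances, not from the week-8 variance.

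The stated endpoint and the stated covariance therefore fit together only if GIS varies equally at each visit, and nothing in the document supports that or contradicts it. If the spread is larger at week 8, the primary interval is too narrow and the test rejects too often. If it is smaller, the interval is too wide and power is lost.

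The fixed effects have a related gap. With only group and visit, the model has one group coefficient for all visits and no separate week-8 difference. Changing the covariance alone would not supply one.

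**Working it through.** **The plan's own figure.** Inputs from section 2.7: 2.72, SD 4.57, 45 per group, 10% dropout. Power is not stated; 80% is assumed because it reproduces the result. Section 2.7 words 2.72 as the mean change in both groups, but N reproduces only if 2.72 is read as the between-group difference.

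- n = 2 × (1.960 + 0.842)² × 4.57² / 2.72² = 44.3, so 45 per group.
- 45 / 0.9 = 50 per group, 100 in total. This agrees with the plan.

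**Standard error of the week-8 contrast.** Take complete data, n per group, and a group-by-visit term added so that the contrast exists. Completeness is a fair approximation, since section 2.8.2 fills gaps by LOCF. Let r = SD(week 4) / SD(week 8).

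- The estimate is the difference of the week-8 means, with true variance 2·SD8² / n.
- Compound symmetry reports 2 × (SD4² + SD8²)/2 / n.
- Reported SE / true SE = √((r² + 1)/2).
- Type I error = 2 × (1 − Φ(1.96 × ratio)).

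| r (assumed) | SE ratio | SE error | Type I error |
|---|---|---|---|
| 0.8 | √0.820 = 0.906 | −9% | 7.6% |
| 0.9 | √0.905 = 0.951 | −5% | 6.2% |
| 1.0 | 1.000 | 0% | 5.0% |
| 1.1 | √1.105 = 1.051 | +5% | 3.9% |
| 1.2 | √1.220 = 1.105 | +10% | 3.0% |

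**Simulation check.** 100,000 null trials per setting, 50 per group, within-participant correlation 0.6, t with 98 degrees of freedom. At r = 0.8 the pooled-variance test has size 7.5%, at r = 1 it has 4.9%, and at r = 1.25 it has 2.6%. Using the week-8 variance alone, as an unstructured covariance does, the size stays near 5% (5.0% to 5.1% at these three ratios).

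**If screening were also a response visit** (not stated), three variances are averaged:

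- SDs 0.7 : 0.9 : 1 give ratio √((0.49 + 0.81 + 1)/3) = 0.876 and 8.6% by formula (8.3% simulated, correlation 0.5).
- SDs 1.2 : 1.1 : 1 give 3.0% simulated.

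**Power on the conservative side.** Take 4.57 as the week-8 SD of the analysed response, with 45 per group.

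- The standardised difference is 2.72 / (4.57 × √(2/45)) = 2.82.
- With a correct SE, power is Φ(2.82 − 1.96) = 80.6%.
- At r = 1.2 it is Φ(2.82 − 1.96 × 1.105) = Φ(0.66), about 74%.

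**The model exactly as listed.** Without group-by-visit, the group coefficient in balanced data is the average of the visit differences. Its test had size 4.8% to 5.1% at every SD ratio simulated. It answers a different question, however. If the week-4 difference is 75% of a week-8 difference of 2.72, the model estimates (0.75 + 1)/2 × 2.72 = 2.38. At 50% it estimates 2.04.

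**The case against.** A reader might infer that the wording forces a common variance and that the primary test is therefore not at 5%. The documents do not support that, for three reasons.

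- **The covariance is not fully fixed.** The model is called an MMRM, and a random participant term does not exclude visit-specific residual variances. The full protocol or analysis plan may give a structure. This stands against *forces*. It does not remove the point, because the article does name a within-participant term, and an analyst coding that term with SAS defaults would obtain compound symmetry.
- **Unequal variances are not shown.** With equal SDs the size is 5%. The direction is also open. Differing responses to treatment could widen the spread, while improvement towards the floor of a bounded score could narrow it. The severity criterion for entry is on the VAS (section 2.2.1), with no GIS threshold, so its effect on screening GIS variance is unknown. All of this stands, which is why the figures are an assumed range and the 8.6% case is only an illustration.
- **The error rates belong to a contrast that the listed model does not contain.** This also stands: the test as listed holds about 5% in complete data. But that test is not of the week-8 difference. Once the group-by-visit term is added to obtain that difference, the covariance assumption matters.

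**Conclusion.** The point holds conditionally. As described, the model does not deliver the week-8 difference that the plan names as primary. If a group-by-visit term is added while the random intercept remains the only covariance term, the type I error of the week-8 test depends on the unknown ratio of GIS SDs across visits: about 7.5% to 3.0% for a week-4 SD of 0.8 to 1.2 times the week-8 SD, and 5% if they are equal. This rests on complete data, two response visits and assumed SD ratios. The size is moderate and the direction unknown, but it concerns the trial's only unadjusted primary test. The remedy is nearly free and should be settled before outcome data are seen by group, since choosing a covariance afterwards could move the primary p-value.

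**What to change.** Replace the model sentence in section 2.8.2 with one that specifies:

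- fixed effects of group, visit and group-by-visit;
- repeated visits within participant with an unstructured covariance, in place of the random participant term;
- REML with Kenward-Roger degrees of freedom;
- heterogeneous compound symmetry as the fallback if the model does not converge;
- the week-8 group difference from this model as the primary estimate.

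In PROC MIXED the covariance part is `REPEATED visit / SUBJECT=participant TYPE=UN` with `DDFM=KR`, and no `RANDOM participant` line. Both parts are needed: an unstructured covariance with only group and visit still gives one group coefficient common to all visits.

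The cost is a short change of wording and code, with no extra participants. Compound symmetry has 2 covariance parameters. Unstructured has 3 for two visits, or 6 if screening is a response, so 1 or 4 more, which 100 participants support. If the variances are in fact equal, almost nothing is lost.

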#### Demographic, sociological data, and other pre-treatment participant characteristics

2.8.1

Summary statistics for demographic and sociological variables, as well as pre-treatment participant characteristics, will be presented for each group. Depending on the normality of the data distribution, continuous variables will be analyzed using either the paired t-test or the Wilcoxon signed-rank test, whereas categorical variables will be analyzed using the chi-square test or Fisher’s exact test. If baseline characteristics show statistically significant differences between groups despite randomization, these variables will be included as covariates in the Mixed Model for Repeated Measures (MMRM) for the primary efficacy analysis to statistically adjust for potential confounding effects.

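### The primary MMRM, as stated, estimates a group difference averaged over visits, whereas the declared primary endpoint is the difference at week 8

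*Protocol article*

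**What the plan says.** Section 2.8.2 fixes the target: "The primary efficacy endpoint is the between-group difference in the GIS score at week 8 (ACCORD vs. DISCORD"). The next sentence fixes the model: the endpoint is "analyzed using the MMRM, with treatment group and visit time as fixed factors and participant as a random factor".

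Three other places bear on how that model is read.

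- Table 1, row "Gastrointestinal Symptom Score": marks at screening, week 4 and week 8, with none at the week 0 visit. The screening score is therefore the only pre-treatment value.
- Section 2.8.1, on baseline variables that differ significantly between groups: "these variables will be included as covariates in the Mixed Model for Repeated Measures (MMRM) for the primary efficacy analysis". No other route for baseline data into the model is given.
- Section 2.8.2, on exploratory subgroups: "Effect modification will be explored using treatment-by-subgroup interaction terms within the mixed model". This is the only interaction named anywhere in the article.

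Section 2.7 sizes the trial on the change in GIS after 8 weeks.

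**The concern.** The endpoint is a difference at one time point. A model with main effects of group and visit and a participant random effect has one group coefficient, and that coefficient is common to all visits. Without a group-by-visit term, the model has no parameter for the week-8 difference in particular.

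Week 4 must be among the responses, since otherwise a visit factor has nothing to do. Whether the screening score is also a response is not stated. If it is, a visit with an expected group difference of zero enters the average, and any real treatment effect is diluted whatever its time course.

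This is the trial's only confirmatory test. Two analysts could fit different models from these two sentences, one with a week-8 contrast and one with an overall group effect, and reach different conclusions.

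**Working it through.** **Inputs from the article.** Two-sided 5% (section 2.8). A figure of 2.72 with SD 4.57, 45 per group, 10% dropout and 100 in total (section 2.7). GIS at screening, week 4 and week 8 (Table 1).

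**Inputs assumed.** Power is not stated, so 80% is taken. Section 2.7 gives 2.72 as the mean change "in both the ACCORD and DISCORD groups is assumed to be 2.72, with a standard deviation of 4.57"; it is read here as the between-group difference, the reading that reproduces the sample size. The week-4 effect as a share f of the week-8 effect, and the within-participant correlation ρ, are not in the document.

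**Step 1: the plan's own figure.** n per group = 2 × [(1.960 + 0.842) × 4.57 / 2.72]² ≈ 44.3, rounded up to 45. Then 45 / 0.90 = 50 per group, 100 in total. This agrees with section 2.7. With 45 per group, a two-sample t-test on the week-8 difference has 79.7% power.

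**Step 2: what the stated model estimates.** With balanced data (nearly so here, because last observation carried forward fills later visits) and a participant random intercept, the group coefficient in a group + visit model is the unweighted mean of the visit-specific differences. Simulated data with the week-4 effect at half the week-8 effect confirm this:

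| Responses | Observed differences by visit | Group + visit | Group × visit, at week 8 |
|---|---|---|---|
| Screening, weeks 4 and 8 | 0.09, 1.81, 2.73 | 1.54 | 2.73 |
| Weeks 4 and 8 | 1.20, 2.13 | 1.66 | 2.13 |

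**Step 3: responses at weeks 4 and 8.** Target = 2.72 × (1 + f)/2. SD of the two-visit mean = 4.57 × √[(1 + ρ)/2], which at ρ = 0.6 is 4.09. At 45 per arm:

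| f | Target | Power |
|---|---|---|
| 0 | 1.36 | 34.5% |
| 0.5 | 2.04 | 64.9% |
| 1 | 2.72 | 88% |

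Break-even with the week-8 contrast is where (1 + f)/2 = √[(1 + ρ)/2]. So f = 2√0.8 − 1 ≈ 0.79 at ρ = 0.6, and 2√0.7 − 1 ≈ 0.67 at ρ = 0.4. Above that share, averaging gains power.

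**Step 4: screening also a response.** Target = 2.72 × (0 + f + 1)/3, which is 1.36 at f = 0.5. The responses are now raw scores, so 4.57, taken as the SD of change, is converted: raw SD = 4.57 / √[2(1 − ρ)]. The SD of the three-visit mean is the raw SD × √[(1 + 2ρ)/3]. The fair comparator is a week-8 contrast on the same raw scale.

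| ρ | Raw SD | Week-8 contrast, power | Three-visit average, f = 0.5, power |
|---|---|---|---|
| 0.4 | 4.17 | 86% | 51% |
| 0.5 | 4.57 | 80% | 40% |
| 0.6 | 5.11 | 70% | 31% |

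Even at f = 1 the target is only 2.72 × 2/3 = 1.81, because the screening difference has expectation zero.

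**The case against.** The article lists factors and does not say that there are no others. The preceding sentence sets the target at week 8, and the label MMRM commonly goes with a group-by-visit term. A reader may therefore supply the interaction, and a fuller analysis plan, not shown, may contain it. That stands as a reason not to infer that the sponsor has rejected the interaction. It does not remove the point: the article names the terms of its primary model, those terms do not deliver the stated endpoint, and the same section names an interaction where one is intended.

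A reader might also infer that the stated model must cost power. The documents do not support this. They give neither the week-4 effect nor the correlation. With weeks 4 and 8 only and a constant effect, averaging is unbiased and more powerful. Nor do they say that screening GIS is a response, so the 31% to 51% range is conditional on that reading. Setting that range against a flat 80% would mix two scales; the like-for-like comparator is 70% to 86%.

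Finally, a reader might fear false positives. If there is no effect at any visit, the averaged difference is also zero and the type I error is not inflated.

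**Conclusion.** The concern holds as a mismatch between the declared endpoint and the model as stated, and that part needs no numerical assumption. The two quantities coincide only if the effect is the same at every modelled visit. That is possible for weeks 4 and 8 alone, but not for a real effect if the pre-randomisation score is a response.

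The size is illustrative. With weeks 4 and 8 as responses at correlation 0.6, power runs from 35% to 88% as the week-4 share goes from 0 to 100%, against about 80% for the week-8 contrast. If screening is also a response and the week-4 effect is half, power is about 31% to 51%, against 70% to 86% on the same raw scale. All of this rests on reading 2.72 as the between-group difference, on SD 4.57 and on 45 evaluable per arm. The sample-size arithmetic itself is not in question here.

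**What to change.** Amend section 2.8.2 before database lock to:

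- add the group-by-visit interaction to the fixed effects;
- name the ACCORD minus DISCORD contrast at week 8 as the primary test;
- state that GIS at weeks 4 and 8 are the responses, and that the screening GIS score is a covariate whether or not the groups differ on it.

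A baseline-by-visit term and an unstructured within-participant covariance are good practice, but are not needed to target week 8.

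The cost is a sentence or two and no new data. The price is that the week-8 contrast does not borrow from week 4, so some power is forgone if the effect is truly constant. If the full analysis plan already contains these terms, the only action is to bring the protocol text into line with it.

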**Outcomes:**

The primary outcome will be gastrointestinal symptom score. Secondary outcomes will include total dyspepsia symptom score, adequate relief of dyspepsia, overall treatment effect, visual analog scale score, functional dyspepsia–related quality of life, and pattern identification questionnaire results. Exploratory outcomes will include blood and fecal metabolome analysis, fecal and salivary microbiota profiling, and measurements obtained using Korean medicine diagnostic devices (heart rate variability, tongue, pulse, and abdominal diagnosis).

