#### Exploratory evaluation variables

2.5.4

Korean medicine diagnostic devices, including an HRV analyzer, tongue diagnosis device, pulse analyzer, and abdominal examination device, will be used. HRV is a non-invasive tool for assessing health status by measuring sympathetic and parasympathetic activity. Kyung Hee University Hospital at Gangdong will use the SA-6000 (MEDICORE Co., Ltd., Republic of Korea), while Dongguk University Ilsan Oriental Medical Hospital will use the SA-3000NEW (MEDICORE Co., Ltd., Republic of Korea). The tongue diagnosis system (CTS-2000, Daeseong Medical Device, Republic of Korea) will evaluate tongue coating thickness, distribution, and color. The pulse analyzer (DMP-Lifeplus, Daeyo Medi Co., Ltd., Republic of Korea) will provide cardiovascular and pulse wave information. The abdominal examination device (Digital Algometer FPX25, Wagner Instruments, United States) will assess tenderness at nine abdominal acupoints: CV-14, CV-12, left/right ST-20, left/right ST-25, CV-4, and left/right ST-28. Stool and saliva samples will be collected at baseline (week 0) and post-treatment (week 8) for gut microbiome and fecal metabolite profiling and for oral microbiome analysis, respectively.

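### The no-adjustment rule for exploratory outcomes also covers metabolome and microbiome profiling, so the false share among any features flagged at p<0.05 would be uncontrolled (minor)

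*Protocol article*

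**What the plan says.** Section 2.8.2 of the protocol article sets three multiplicity rules. The primary endpoint is tested at 0.05 without adjustment. For the ten secondary efficacy endpoints, "the Benjamini-Hochberg procedure (False Discovery Rate, FDR) will be applied to adjust the" p-values. For everything below that level: "Exploratory outcomes will not be adjusted for multiplicity, and their results will be interpreted as hypothesis-generating".

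The last rule has a wide reach. The Abstract states: "Exploratory outcomes will include blood and fecal metabolome analysis, fecal and salivary microbiota profiling", and adds the Korean medicine diagnostic devices. Section 2.1.1 describes blood, stool and saliva sampling before and after treatment for blood and fecal metabolites and for gut and oral microbiomes. Section 2.5.4, under the exploratory variables, repeats that stool and saliva are taken "for gut microbiome and fecal metabolite profiling and for oral microbiome analysis, respectively".

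The only significance threshold given for any of this is in the opening of Section 2.8: "All statistical analyses will be conducted using two-sided tests with a significance level of 5" per cent.

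**The concern.** Leaving a handful of device measures unadjusted is reasonable. The same sentence also covers four profiling platforms, each of which usually yields many features. If each metabolite or taxon is tested at an unadjusted 5%, the flagged list has no stated error rate. The hypothesis-generating label limits how strongly a result is claimed, but it does not tell the reader what share of the list is likely to be noise.

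The section applies false discovery rate control to ten secondary endpoints and excludes it where the number of tests is likely to be largest. Because the exclusion is stated outright, an analysis plan that used such control for the omics data would depart from the published protocol.

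What is at stake is how the exploratory feature lists can be used. The trial's main result is not affected.

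**Working it through.** **Inputs from the article.** Two-sided 5% level (Section 2.8); 45 evaluable participants per group before the 10% dropout allowance, 100 in total (Section 2.7).

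**Inputs the article does not give, so assumed.** Number of features m; share of features that truly differ, π; standardized difference d of those features. The calculation also assumes that features are tested one at a time between the two groups.

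**Step 1: the plan's own figure.** Section 2.7 says "the mean change in the GIS score after 8 weeks in both the ACCORD and DISCORD groups is assumed to be 2.72". The SD stated there is 4.57. Reading 2.72 as the between-group difference and assuming 80% power, which the section does not state:

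n = 2 × (1.960 + 0.842)² × (4.57/2.72)² ≈ 44.3, rounded up to 45 per group; 45/0.9 = 50 per group, 100 in total.

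The stated figure reproduces on that reading, so 45 per group is used below. The wording of the 2.72 and the unstated power are separate matters and do not bear on this point.

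**Step 2: expected false positives if no feature differs.** 0.05 × m gives 5 for m = 100, 25 for 500, 50 for 1,000 and 100 for 2,000, per platform and contrast. These counts grow with m, but they do not show what share of the flagged features is false.

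**Step 3: power per feature at 45 per group.** Power ≈ Φ(d × √(45/2) − 1.96):

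- d = 0.3: 0.296
- d = 0.5: 0.660
- d = 0.8: 0.967

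**Step 4: false share among features with p<0.05** (ratio of expected counts):

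false share = 0.05(1 − π) / [0.05(1 − π) + power × π]

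| π (truly different) | d = 0.3 | d = 0.5 | d = 0.8 |
|---|---|---|---|
| 1% | 94% | 88% | 84% |
| 5% | 76% | 59% | 50% |
| 10% | 60% | 41% | 32% |
| 20% | 40% | 23% | 17% |
| 30% | 28% | 15% | 11% |

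For example, at π = 1% and d = 0.3: 0.0495/(0.0495 + 0.00296) = 0.94. At π = 30% and d = 0.8: 0.035/(0.035 + 0.290) = 0.11. The number of features m cancels out of this ratio.

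**Step 5: when do false features form the majority?** Setting the share to one half and solving gives approximately π = 0.05/(0.05 + power): 14.5% for d = 0.3, 7.0% for d = 0.5 and 4.9% for d = 0.8. Below these values more than half of the flagged features are false; above them, fewer than half.

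**Step 6: with the fix.** Benjamini-Hochberg at level q holds the expected false share at or below q under independence or positive dependence, whatever π and the power are: 5% at q = 0.05, 10% at q = 0.10.

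**The case against.** The strongest defence is that the quoted sentence carries its own safeguard. Exploratory results without adjustment, labelled hypothesis-generating, are an accepted convention. Adjusting the secondary endpoints, which support claims, but not the exploratory ones follows an evidential hierarchy and is not a contradiction. The article also never says that each metabolite or taxon will be tested separately, or that features at p<0.05 will be listed as different. The omics model may be targeted, multivariate or at community level, and an article may leave that to a fuller document. Finally, Benjamini-Hochberg does not change the ranking of features. It sets a cut-off, which a reader could apply if all p-values were published.

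Much of this stands. It makes the point conditional on feature-level testing and keeps it minor. It does not remove the point, because the article leaves nothing open here: it rules out adjustment for the whole class, and the label gives no error rate for a flagged list.

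A reader might go further and infer that most features at p<0.05 will be false, or that the lists will largely fail to replicate. The documents do not support that, because it depends on π and power and neither is given. One consideration makes few true differences plausible for ACCORD against DISCORD: if recommendations were spread evenly over the three formulas (an assumption), the 2:1:1 scheme would give each formula to a third of each group, so average formula effects would tend to cancel. Pre-post contrasts could carry many more true changes. Nor does the article say that features from this trial will feed a later algorithm. Section 2.1.2 aside, Section 2.1.1 says only that version 1.1 is locked for the study.

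**Conclusion.** The concern holds in a conditional and minor form. The plan rules out multiplicity adjustment for a class that includes four omics platforms. If these are analysed feature by feature at 5%, the false share among flagged features is uncontrolled. Under assumed inputs at 45 per group it lies anywhere from about 11% to about 94%, and it passes one half only if fewer than roughly 5% to 15% of features truly differ. The width of that range is itself the finding: a reader of the results could not tell where in it a given list falls. Neither a majority of false features nor a failure to replicate can be asserted from the document. The primary comparison and the adjusted secondary endpoints are untouched.

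**What to change.** Limit the no-adjustment sentence in Section 2.8.2 to the device measures and add a rule for the omics data, for example:

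*Device measures (HRV, tongue, pulse, abdominal) are reported with unadjusted p-values. Where metabolome or microbiome data are tested at feature level, p-values are adjusted by Benjamini-Hochberg within each platform and contrast. Features are flagged only at q ≤ 0.10, and q-values are reported for every feature. All these results remain hypothesis-generating.*

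The threshold of 0.10 is an example. The sponsor may choose another value, provided that it is fixed before the data are analysed.

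The cost is one or two sentences and a shorter list of flagged features. Section 2.11 requires a formal amendment and approval by both ethics boards for substantial changes to analyses. If this counts as one, that step is an added cost and a reason to make the change before database lock.

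### LOCF is the primary handling of missing GIS scores beside an MMRM that needs no imputation; it shrinks a real week-8 difference and is not reliably conservative

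*Protocol article*

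**What the plan says.** Section 2.8.2 (Statistical analysis and evaluation of efficacy endpoints) defines the primary endpoint as the ACCORD versus DISCORD difference in GIS score at week 8. On the model it says: "The primary endpoint will be analyzed using the MMRM, with treatment group and visit time as fixed factors and participant as a random factor". On missing data it says: "For the primary outcome, missing data will be handled using the last observation carried forward (LOCF) method", and then that "multiple imputation will be applied as a sensitivity analysis to assess the robustness of results under different assumptions regarding missingness". No reason is given for choosing LOCF.

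In Table 1 (Clinical study schedule) the row "Gastrointestinal Symptom Score" is marked at screening, week 4 and week 8 only. Section 2.7 (Sample size calculation) plans for 10% dropout and 100 participants. Section 2.4.2 encourages those who stop treatment to stay for outcome assessments wherever possible, so some week-8 scores may still be missing.

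**The concern.** An MMRM fitted by likelihood takes incomplete records as they are. Under missing at random, a participant seen at week 4 but not at week 8 still contributes, and nothing has to be filled in. Completing the data by LOCF first gives up that property. It substitutes the assumption that a participant's score stays fixed from the last visit onward, which is hard to defend over an 8-week course in which scores are expected to move.

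With three GIS time points there are only two values to carry. A participant lost after week 4 gets the week-4 score at week 8. A participant lost before week 4 gets the pre-treatment score, that is, a change of zero (assuming that the LOCF rule carries pre-treatment values, which the article does not specify). The single confirmatory comparison of the trial is computed from these values.

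**Working it through.** **Plan's own figure.** Section 2.7 says "the mean change in the GIS score after 8 weeks in both the ACCORD and DISCORD groups is assumed to be 2.72", with SD 4.57 and 45 per group. Reading 2.72 as the between-group difference, at two-sided 5% and 80% power (power is not stated; 80% is inferred because it reproduces 45):

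n = 2 × (1.960 + 0.842)² × (4.57 / 2.72)² = 2 × 7.849 × 2.823 = 44.3, rounded up to 45 per group. 45 / 0.90 = 50 per group, 100 in total. The figure reproduces, so 2.72 is used below as the true difference.

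**Formula.** Let M be an arm's mean improvement at week 8, d its dropout proportion, and f the fraction of improvement present at the carried visit. If dropout is unrelated to outcome within an arm, the LOCF mean is M(1 − d) + d·f·M = M[1 − d(1 − f)]. If everyone who drops out has a week-4 score, f is the week-4 fraction. If everyone drops out before week 4, f = 0. These two cases bound the result.

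**Assumptions not in the documents.** Half of the improvement is present by week 4 (f = 0.5); mean improvement is 8.00 in ACCORD and 5.28 in DISCORD (difference 2.72), or 6.64 in each arm when there is no true difference; and the split of dropout between arms.

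**Equal dropout, 10% in each arm.**
- Week 4 carried: 2.72 × (1 − 0.10 × 0.5) = 2.58, a loss of 0.14.
- Screening carried: 2.72 × (1 − 0.10) = 2.45, a loss of 0.27.
- No true difference: both arms shrink equally, so the bias is 0.

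Here the levels 8.00 and 5.28 do not matter, because only their difference enters.

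**Unequal dropout, for illustration.** 4% and 16% of 50 are 2 and 8 participants, which is 10% overall.

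| True difference | Dropout ACCORD / DISCORD | Week 4 carried | Screening carried |
|---|---|---|---|
| 0 (6.64 in each arm) | 4% / 16% | 6.64 × (0.98 − 0.92) = 0.40 | 6.64 × (0.96 − 0.84) = 0.80 |
| 2.72 | 16% / 4% | 8.00 × 0.92 − 5.28 × 0.98 = 2.19 | 8.00 × 0.84 − 5.28 × 0.96 = 1.65 |
| 2.72 | 4% / 16% | 8.00 × 0.98 − 5.28 × 0.92 = 2.98 | 8.00 × 0.96 − 5.28 × 0.84 = 3.24 |

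The false difference of 0.40–0.80 is 15–29% of 2.72.

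**Simulation under different assumptions.** 8,000 trials per scenario, 50 per arm, SD 4.57. Assumed: DISCORD improvement 5 points, 60% of it by week 4, within-patient correlation 0.6, half of dropout before week 4, later dropout likelier in poor week-4 responders. A two-sample comparison of LOCF-completed week-8 change was set against a likelihood estimate from observed data with a separate mean for each group at each visit.

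| True difference | Dropout ACCORD / DISCORD | LOCF estimate | LOCF rejection rate | Likelihood estimate | Likelihood rejection rate |
|---|---|---|---|---|---|
| 2.72 | 10% / 10% | 2.51 | 73% | 2.71 | 80% |
| 2.72 | 5% / 15% | 3.03 | 88% | 2.73 | 80% |
| 2.72 | 15% / 5% | 2.04 | 55% | 2.72 | 80% |
| 0 | 10% / 10% | −0.02 | 4.9% | −0.03 | 4.7% |
| 0 | 5% / 15% | 0.42 | 7.5% | 0.02 | 5.0% |
| 0 | 15% / 5% | −0.40 | 7.3% | 0.00 | 5.1% |

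The pattern agrees with the closed form: attenuation under equal dropout, no bias under the null, and bias in either direction once dropout is unequal.

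**The case against.** **The effect is modest at the planned dropout.** This stands. At 10% in each arm the loss is 5–10% of 2.72, and there is no inflation of type I error. The larger figures need an imbalance that the documents do not report.

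**Unequal dropout is not established.** A reader might infer that dropout is bound to be higher in DISCORD because the trial is open-label and that arm gets a formula the algorithm did not choose. The documents do not support going that far. Both arms receive the same three approved formulas on the same regimen (section 2.4.1). The article does not say that participants are told which formula was recommended, and section 2.4.2 asks those who stop to remain for assessment. What remains is possibility: section 2.4.2 lists marked symptom deterioration among the reasons for discontinuing, and section 2.4.3.2 lets the investigator withdraw participants who use new dyspepsia treatment.

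**Multiple imputation is already planned.** It could expose a result driven by LOCF, which lessens the harm. The primary p-value would still be the LOCF one.

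**Standard errors.** A reader might also infer that filled-in values make the standard errors too small. That is not demonstrated. In a simulated two-sample comparison of LOCF-completed change (50 per arm, correlation 0.6, random dropout of 10% in each arm), the mean model standard error was 0.933–0.956 against an empirical SD of 0.944–0.961. It was understated by at most about 2%, with null rejection of 4.8–5.2%. This was not the full MMRM, but it shows no material fault. The excess rejections above come from bias.

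**Type of imputation.** A reader might want the multiple imputation required to be missing-not-at-random. The article already promises different assumptions about missingness and does not confine itself to missing at random. Such detail is commonly left to the analysis plan.

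**Conclusion.** The point holds as a fault in the choice of primary missing-data method. The article pairs an MMRM with an imputation that the model does not need, gives no reason, and thereby rests the week-8 comparison on an assumption of no change after the last visit.

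At the document's own 10% dropout, assumed equal in both arms and with half of the improvement present by week 4, a true 2.72 is reported as about 2.45–2.58, with no bias if there is no true effect. If dropout differs by arm, the direction depends on which arm loses more participants, so LOCF cannot be defended as conservative. The 0.40–0.80 false difference illustrates this under an assumed 4% / 16% split and 6.64 points of improvement per arm; it is not a forecast. Missing at random is itself an assumption, and testing it is the proper task of the planned multiple imputation.

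**What to change.** In section 2.8.2, replace the LOCF sentence with wording such as: The primary MMRM will be fitted by REML to all observed GIS scores, without imputation, under a missing-at-random assumption. Delete LOCF, or keep it as a labelled sensitivity analysis beside the multiple imputation already planned.

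One dependency should be checked at the same time. The likelihood results above use a separate mean for each group at each visit, whereas the article lists only group and visit as fixed factors. The week-8 contrast should be confirmed as what the model estimates; that is a separate point from LOCF.

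The cost is wording: no new data, no extra visits, and no change to 45 per group or the total of 100. Section 2.11 treats changes to analyses as formal amendments needing approval by both IRBs and a registry update. The change should therefore be made before database lock.
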